## 18. ADVERSE EVENTS

### 18.1 Definitions

#### 18.1.1 Adverse Event

An AE is any untoward medical occurrence in a research participant, whether or not considered drug related which occurs during the conduct of a clinical trial. Any change in

clinical status, ECGs, routine labs, x-rays, physical examinations, etc., that is considered clinically significant by the PI is considered an AE.

Blood pressure (BP) and heart rate (HR) must meet the following criteria to be considered an AE for the purposes of this study:

- Systolic blood pressure (SBP) >140 mmHg or diastolic blood pressure (DBP) >90 mmHg on three separate readings
- Clinically significant decrease in BP
- Heart rate (HR) >100 beats per minute (BPM)
- Clinically significant decrease in HR

The AE terms listed below are MedDRA Preferred Terms to be used in classifying abuse liability

AEs when deemed appropriate by the PI (or designee):

- Euphoria-related terms: euphoric mood, elevated mood, feeling abnormal, feeling drunk, feeling of relaxation, dizziness, thinking abnormal, hallucination, inappropriate affect
- Terms of impaired attention, cognition, and mood: somnolence, mood disorders, and disturbances
- Dissociative/psychotic terms: psychosis, aggression, confusion, and disorientation

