#### Cardiovascular Monitoring During Dosing Session

Blood pressure and heart rate will be obtained at 30, 60, 90, 120 minutes, 4, 6, and 7 hours after drug administration. Participants will not be discharged until after the 7-hour blood pressure and heart rate assessments have been completed. Measurements must be collected within +/-10 minutes of the scheduled time point. Measurements will be conducted by trained study personnel. Blood pressure measurements should occur after the participant has been recumbent a minimum of 10 minutes.

**Table 3:** Blood Pressure Monitoring during Dosing

| Cardiovascular Monitoring (Blood Pressure): Dosing Session                            |                                                                                                                                    |
|----------------------------------------------------------------------------------------------|------------------------------------------------------------------------------------------------------------------------------------|
| The following Blood Pressure safety parameters have been established for the dosing session: |                                                                                                                                    |
| Result                                                                                | Instructions                                                                                                                |
| SBP $\leq$ 170 mmHg and DBP $\leq$ 95 mmHg                                                   | No additional follow up needed, take BP at next scheduled time point.                                                              |
| SBP $>$ 170 and $<$ 200 mmHg or DBP $>$ 95 and $<$ 110 mmHg                                  | Repeat every 5 minutes for a total of three readings over 15 minutes.
• If three or more readings are elevated consult with the |

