| SBP $\geq$ 200 mmHg or
DBP $\geq$ 110 mmHg | 
Consult with the study physician for further evaluation and follow up. Medication and medication administration is at the clinical judgment of the Study Physician and is not protocolized. The following medication administration is a recommendation; however, the Study Physician may treat the participant based on his or her own judgement and with the medications available on site.
 
 
• The participant may be treated with sublingual nitroglycerin 0.4 mg
 
• If blood pressure readings do not decrease below these thresholds after 5 minutes, the same dose of nitroglycerin will be administered
 
• A third dose of nitroglycerin will be given after another 5 minutes, if readings remain elevated above these levels (maximum dose is 0.4 mg x 3)
 
• If blood pressure remains <math>\geq</math>200 systolic or <math>\geq</math>110 diastolic, at the judgment of the study physician, the participant will be treated with oral clonidine (e.g., 0.1 mg) and the Study Physician will evaluate whether transport to the emergency room is necessary..
 
 |
|-----------------------------------------------|----------------------------------------------------------------------------------------------------------------------------------------------------------------------------------------------------------------------------------------------------------------------------------------------------------------------------------------------------------------------------------------------------------------------------------------------------------------------------------------------------------------------------------------------------------------------------------------------------------------------------------------------------------------------------------------------------------------------------------------------------------------------------------------------------------------------------------------------------------------------------------------------------------------------------------------------------------------------------------------------------------------------------------------------------------------------------------------------------------------------------------------------------------------------------------------------------------|

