### 18.1.3 Solicited Adverse Events

The following solicited AEs will be collected:

Visual perceptual effects (Periods 3-4) will be solicited by asking the following questions: 1) *Since your dosing session have you experienced any uncontrolled or disturbing return of study drug effects?*, and 2) *Since your dosing session have you experienced any visual distortions (e.g. geometric hallucinations, false perceptions of movement in the peripheral visual fields, flashes of color, intensified color, trails for images of moving objects, positive after-images, halos around objects)?* If a participant reports “Yes” to any of the above questions a study psychologist or psychiatrist will follow up for further assessment/diagnosis.

Additional solicited AEs include:

- Active suicidal ideation identified through MADRS and verified by clinical assessment.
- Headache; and
- Nausea and
- Elevated blood pressure (BP) as defined by systolic blood pressure (SBP) >140 mmHg or diastolic blood pressure (DBP) >90 mmHg on three separate readings and requiring medication; and

- Elevated heart rate (HR) as defined as >100 beats per minute (BPM) and requiring medication; and
- Drug and alcohol abuse/misuse as defined by the MINI; substance and alcohol use disorders as defined by the MINI; or drug overdose with suicidal intent.

Monitoring for suicidality will be ongoing throughout the duration of the study using MADRS. If at any time during an evaluation or follow up there is concern a participant is suicidal study staff will follow standard of care procedures for managing suicidality, eg as described in <https://psykiatristod.se/regionala-varldprogram/depression>.

To assess for headache after psilocybin administration, participants will be asked if they have or experienced a headache during Period 3, and these will be classified as a migraine, tension headache, or other headache. On the dosing day, participants reporting headache will be encouraged to take non-steroidal anti-inflammatory agents or acetaminophen at home, if needed.

Visual perceptual effects, suicidal ideation verified by clinical assessment, headache, nausea, and overdose with suicidal intent will be reported through normal AE/SAE mechanisms.

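### The adverse event definitions make no provision for a single blood pressure reading in the SBP ≥200 or DBP ≥110 row of Table 3, or one that leads to rescue medication, so a brief treated spike can go unrecorded as an AE

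*Protocol*

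**What the plan says.** Section 18.1.1 begins with a general clause: any change in "clinical status, ECGs, routine labs, x-rays, physical examinations, etc., that is considered clinically significant by the PI is considered an AE". It then sets a condition for vital signs: "Blood pressure (BP) and heart rate (HR) must meet the following criteria to be considered an AE for the purposes of this study". For a rise in blood pressure the list holds one criterion: "Systolic blood pressure (SBP) >140 mmHg or diastolic blood pressure (DBP) >90 mmHg on three separate readings". The readings need not be consecutive or fall within a time window. A fall in blood pressure is left to clinical significance, and a heart rate above 100 counts without a repeat.

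Section 18.1.3 defines the solicited blood pressure event with the same limits, "on three separate readings and requiring medication". The solicited list in the synopsis does the same.

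Table 3 (section 9.3.2, cardiovascular monitoring during the dosing session) has three rows:

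- **SBP ≤170 and DBP ≤95:** "No additional follow up needed, take BP at next scheduled time point".
- **SBP above 170 and below 200, or DBP above 95 and below 110:** repeat every 5 minutes, to three readings over 15 minutes.
- **SBP ≥200 or DBP ≥110:** consult the study physician, who may give medication. No number of readings is required first. After treatment, "If blood pressure readings do not decrease below these thresholds after 5 minutes, the same dose of nitroglycerin will be administered". The thresholds meant are 200/110, not 140/90.

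There are seven scheduled post-dose readings: at 30, 60, 90 and 120 minutes and at 4, 6 and 7 hours.

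**The concern.** The definition of an AE and the treatment table use different triggers. The definition counts readings above a low limit. The table's highest row acts on one reading above a high limit. Nothing in 18.1.1 or 18.1.3 says that a reading which reaches that row, or which is medicated, counts in its own right.

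Section 18.2 grades an event that requires intervention as at least moderate. A medicated spike would therefore be at least moderate if it were an AE, yet it can fall outside the definition while small untreated rises fall inside it.

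This matters because section 5.4.2 makes the incidence of AEs, TEAEs and solicited AEs, each also by severity, between-group safety endpoints. Section 17.1.1 lists raised blood pressure and heart rate among the physiological adverse events most often reported with psilocybin.

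**Working it through.** The protocol states no figure to reproduce here. The check applies the 18.1.1 rule to reading sequences that are possible under Table 3.

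**Rule (18.1.1):** let n be the number of readings with SBP >140 or DBP >90. The rise is an AE if n ≥ 3.

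**Sequences:** the values are assumed for illustration and are not trial data. In A to D the reading of 205/112 is in the ≥200/≥110 row, is treated, and is re-read at 5 minutes.

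| | Readings in order (all later ones normal) | n | AE under 18.1.1? |
|---|---|---|---|
| A | 132/82, 205/112, 138/86 | 1 | No |
| B | 132/82, 205/112, 165/92, next scheduled 138/88 | 2 | No |
| C | 132/82, 205/112, 165/92, next scheduled 150/88 | 3 | Yes |
| D | 150/88, 205/112, 165/92 | 3 | Yes |
| E | 142/85 at three scheduled readings, no treatment | 3 | Yes |

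**Table 3 does not force a third qualifying reading.** In B the 5-minute value of 165/92 is in the lowest row, so nothing more is due until the next scheduled time. By then the pressure may be 140/90 or below.

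**The solicited route does not help.** Section 18.1.3 needs n ≥ 3 and medication. A and B meet the medication part and fail on n. E meets n but has no medication, so it is an AE and not a solicited AE.

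**The gap is limited.** C and D show that a fall below 200/110 does not by itself remove the event. It is missed only when n ≤ 2 over all readings.

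**Scale of one missed case:** with 15 per group (section 16.1), 1/15 = 0.067, or 6.7 percentage points of that arm's incidence. This is the effect of one hypothetical participant and not an estimate of how many are missed.

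**The case against.** The strongest reply is that the gap is narrow and other text may cover it.

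- **Many readings can count.** Seven scheduled readings plus any repeats are eligible and need not be consecutive. If the re-check is still in the middle or highest row, more readings follow. This stands, and it is why the point is confined to n ≤ 2. Extra readings help only if they too exceed 140/90.
- **The investigator's judgement.** The general clause in 18.1.1 makes any clinically significant change an AE. But a specific condition worded as must follows it, and for blood pressure that list gives a judgement route to falls and none to rises. If the general clause prevails, the condition has no force. If the condition prevails, the spike is excluded. Sites could record the same event differently.
- **The serious event route.** Section 18.1.4 includes important medical events that need intervention, with no count of readings. It could capture some spikes, but it too depends on judgement.
- **Other records.** The rescue drug, its time and its reason go on the concomitant medication log (section 9.3.2), and section 16.4.6 lists such drugs. The event is therefore traceable, but a listing does not enter AE incidence.

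A reader might go further and infer that any treated spike that falls is excluded, or that the main cardiovascular risk is under-counted and the comparison biased toward no difference. The documents do not support this. Sequences C and D are AEs. A sustained unmedicated SBP of 195 would be an AE under 18.1.1, because the middle row calls for three readings; it is outside the solicited category only. The rule also counts mild sustained rises, and no rate of brief severe spikes is given, so no net direction follows.

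Nor can one say that the 140/90 limit hardly matters for the solicited event. The end-of-dosing-day table in 9.3.2 allows medication after three consecutive readings at or above 140/90.

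**Conclusion.** The point holds as a gap in the recording rule. Read literally, sections 18.1.1 and 18.1.3 and the synopsis leave a single reading at SBP ≥200 or DBP ≥110, treated and followed by at most one other reading above 140/90 that day, outside both the AE and the solicited AE. Three untreated readings of 142 are inside the AE definition.

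This rests on reading must as binding and on no unscheduled reading above 140/90 making up the count. Each missed participant is worth 6.7 percentage points in an arm of 15. How often this would happen, and which way any net bias would run, cannot be worked out from the documents. The case for a change is that the definitions and Table 3 disagree on a known drug effect that feeds stated safety endpoints, and that the correction is cheap.

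**What to change.** Reconcile sections 18.1.1 and 18.1.3 and the solicited list in the synopsis with Table 3. State, as a recording rule only, that any dosing-session rise in blood pressure that leads to rescue medication, or that falls in the SBP ≥200 or DBP ≥110 row of Table 3, is recorded as an AE and as the solicited blood pressure AE, whatever the number of readings. Keep the three-reading rule for all other rises. Leave every clinical threshold and action as it is. Heart rate needs no such addition, because 18.1.1 and 18.1.3 already count it without repeat readings.

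The cost is a sentence or two in each place and a check in the eCRF, with no new measurement, visit or staff. The downside is a slightly higher reported AE count.

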### 18.1.2 Treatment Emergent Adverse Events

Treatment emergent adverse events are undesirable events not present prior to medical treatment, or an already present event that worsens either in intensity or frequency following the treatment. Events with an onset after study drug administration will be considered TEAEs.

### 18.1.3 Solicited Adverse Events

The following solicited AEs will be collected:

Visual perceptual effects (Periods 3-4) will be solicited by asking the following questions: 1) *Since your dosing session have you experienced any uncontrolled or disturbing return of study drug effects?*, and 2) *Since your dosing session have you experienced any visual distortions (e.g. geometric hallucinations, false perceptions of movement in the peripheral visual fields, flashes of color, intensified color, trails for images of moving objects, positive after-images, halos around objects)?* If a participant reports “Yes” to any of the above questions a study psychologist or psychiatrist will follow up for further assessment/diagnosis.

Additional solicited AEs include:

- Active suicidal ideation identified through MADRS and verified by clinical assessment.
- Headache; and
- Nausea and
- Elevated blood pressure (BP) as defined by systolic blood pressure (SBP) >140 mmHg or diastolic blood pressure (DBP) >90 mmHg on three separate readings and requiring medication; and

- Elevated heart rate (HR) as defined as >100 beats per minute (BPM) and requiring medication; and
- Drug and alcohol abuse/misuse as defined by the MINI; substance and alcohol use disorders as defined by the MINI; or drug overdose with suicidal intent.

Monitoring for suicidality will be ongoing throughout the duration of the study using MADRS. If at any time during an evaluation or follow up there is concern a participant is suicidal study staff will follow standard of care procedures for managing suicidality, eg as described in <https://psykiatristod.se/regionala-varldprogram/depression>.

To assess for headache after psilocybin administration, participants will be asked if they have or experienced a headache during Period 3, and these will be classified as a migraine, tension headache, or other headache. On the dosing day, participants reporting headache will be encouraged to take non-steroidal anti-inflammatory agents or acetaminophen at home, if needed.

Visual perceptual effects, suicidal ideation verified by clinical assessment, headache, nausea, and overdose with suicidal intent will be reported through normal AE/SAE mechanisms.

#### 18.1.4 Serious Adverse Events

An SAE as determined by the PI or the Sponsor is any event that results in any of the following outcomes:

1. Death
2. Life-threatening AE (Life-threatening means that the study participant was, in the opinion of the PI or Sponsor, at immediate risk of death from the reaction as it occurred.)
3. Inpatient hospitalization or prolongation of existing hospitalization
4. Persistent or significant incapacity or substantial disruption of the ability to conduct normal life functions
5. Congenital abnormality or birth defect
6. Important medical event that may not result in one of the above outcomes but may jeopardize the health of the study participant or require medical or surgical intervention to prevent one of the outcomes listed in the above definition of serious event.

#### 18.1.5 Definition of Terms

**Life threatening:** A life threatening AE is defined as an event in which the participant is at risk of death at the time of the event. It does not refer to an event that hypothetically might have caused death if it was more severe.

**Disability:** A disabling AE is defined as a substantial disruption of a person's ability to conduct normal life functions.

**Important Medical Event:** Examples of such events include invasive or malignant cancers, intensive treatment in an emergency room or at home for allergic bronchospasm, blood dyscrasias or convulsions that do not result in hospitalization, or development of drug dependency or drug abuse.

## 18.2 Guidelines for Assessing Intensity of an Adverse Event

The PI should use the following definitions when assessing Intensity of an AE:

- **MILD:** Participant is aware of symptoms or has minor findings, but tolerates them well and no or minimal intervention required
- **MODERATE:** Participant experiences enough symptoms or findings to require intervention
- **SEVERE:** Participant experiences symptoms or findings that require significant intervention

## 18.3 Guidelines for Determining Causality of an Adverse Event

The PI and Medical Monitor will use the following question when assessing causality of an AE due to the study drug or as a result of study participation: Is there a reasonable possibility that the study drug or procedure caused the event?

A reasonable possibility implies there is evidence that the specific event was caused by the study drug or as a result of participation in the study. An affirmative answer designates the event as a suspected adverse reaction, and the AE is therefore considered “related.” If the answer is no, then the AE is considered “unrelated.”

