#### **16.4.6 Safety Analyses**

All recorded AEs will be coded using MedDRA and presented by SOC and preferred term with number of subjects, percentages and number of events overall and by study period. The worst severity will be used for each event. TEAEs, solicited AEs, SAEs and AEs related to treatment will be summarized similarly. AEs leading to discontinuation from the study will be listed and tabulated.

All concomitant medications will be listed. Safety data collected for the period from Screening through the Baseline assessment and during the Preparation Phase will be presented separately from post-dose safety data (treatment emergent).

All solicited AEs observed in randomized participants who received psilocybin or niacin placebo will be reported.

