## **17.6 Risks Associated with lumbar puncture**

Lumbar puncture (LP) for CSF collection will be performed at two occasions some 2-4 weeks apart (all together ca 10 mL of CSF) and after MR-imaging of the head, which will enable identifying signs of increased intracranial pressure. LP will be performed in the L4-L5 or adjacent lumbar intra columnar spaces, with the participant either lying down on the side, or sitting, with maximal kyphosis in the lumbar segment, and in local anaesthesia. Still there is a risk of post LP headache. The first line of treatment for post-LP headache is recumbence, hydration and analgesics as needed. However, if post-LP headache persists after a day of such treatment, administration of an epidural blood patch will be considered.

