## 18.6 Regulatory Reporting

All SAEs will be reported by PI or designee, whether or not considered causally related to psilocybin, placebo or to the radioligand/ study procedure(s). SAEs will be collected in a list, which will be sent to the Swedish Medical Products Agency (MPA) and the IRB once a year until the study is on-going. In the case of a SAE, an assessment of the security of the subjects participating in the study will also be included. For fatal or life-threatening AEs where important or relevant information is missing, active follow-up will be undertaken immediately by the investigator by interview and/or physical examination and follow-up as deemed necessary by the investigator. In order to enable specific treatment of drug related AEs unblinding will be possible via the investigator (24 hrs phone accessibility). Unblinding will be only performed if it is necessary for the investigator to have this knowledge when making a decision on how to treat an AE. In case the knowledge will not affect treatment choice the blind will not be opened.

The following information is mandatory for the initial report:

- Subject study ID
- Study treatment
- Start date (time, if relevant) of the study treatment
- Brief description of the event (diagnosis)
- Start date (time, if relevant) of the event
- Seriousness criteria
- Causality assessment

The investigator has to inform sponsor of all SAEs within 24 hours of the investigator's awareness using a Safety-approved report form (e.g., specified SAE form or local regulatory form) and perform follow-up activities. These will include interview and physical examinations as deemed relevant and continue as long as is deemed clinically relevant by the investigator.

SLSO is responsible for the recording and reporting of any suspected unexpected serious adverse reactions (SUSARs) to the regional ethics committee and to the Eudravigilance system, clinical trials module. Life-threatening or fatal SUSARs will be reported as soon as possible but at latest within 7 days after the sponsor has become aware of it. Relevant follow-up information will be reported within 8 additional days. Other SUSARs will be reported as soon as possible but at latest within 15 days after the sponsor has become aware of it.

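### A single causality question covers study drug and study procedures, so complications of post-dose procedures can be tabulated as treatment-related and, if serious and unexpected, handled as suspected drug reactions

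*Protocol*

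**What the plan says.** **The rule.** Protocol section 18.3 tells the PI and medical monitor to ask "Is there a reasonable possibility that the study drug or procedure caused the event". It explains the standard in the same joint terms: "A reasonable possibility implies there is evidence that the specific event was caused by the study drug or as a result of participation in the" [trial]. The consequence of a yes is fixed: "An affirmative answer designates the event as a suspected adverse reaction, and the AE is therefore considered" related. There is no second item for which of the two causes was meant.

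**Where the flag is used.** Protocol section 16.4.6 plans that "TEAEs, solicited AEs, SAEs and AEs related to treatment will be summarized similarly", that is, by system organ class and preferred term. Section 18.6 makes the sponsor responsible for reporting SUSARs, and its mandatory content for the initial SAE report includes one causality item.

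**What happens to patients after the capsule.** Section 9.5.1 places the second PET scan, second lumbar puncture and second blood sampling around Day 15 (±7 days). Section 12 requires arterial cannulation at each PET scan. Section 9.4.1 repeats the MRI at Day 1 (+3 days). All of this is the same in both arms.

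**Known complications.** Section 17.5 lists bruising, infection, bleeding and fainting for blood sampling. On lumbar puncture, section 17.6 says "Still there is a risk of post LP headache". Section 17.7 lists infection and thrombophlebitis at the tracer injection site.

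**The concern.** A treatment-related AE table is meant to show what investigators attribute to psilocybin as against niacin. Under section 18.3 a bruise from the arterial line or a headache after the second lumbar puncture gets the same label as an acute drug reaction. Such events should occur about equally in both arms. They therefore raise the related-AE count in each arm, niacin included, and pull the comparison towards no difference.

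The second consequence concerns expedited reporting. A SUSAR is by definition a suspected reaction. Section 18.3 makes every procedure-caused event a suspected adverse reaction, so one that is also serious and unexpected meets the wording for a suspected reaction to the capsule. The radioligand is caught in the same way, although section 11.1 classes it as a non-investigational product.

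**Working it through.** The plan states no figure on this point, so there is none to reproduce. The check is a reading of the sections side by side, followed by an illustration on assumed rates.

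**Step 1: does any other text separate the causes?** Section 18.6 names psilocybin, placebo and the radioligand or study procedures as distinct possible causes, but only to say that all SAEs are reported whatever their cause. It creates no separate attribution. Section 18.3 remains the only definition of relatedness.

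**Step 2: which events reach the post-dose table?** Section 18.1.2 treats any event with onset after study drug administration as a TEAE, so complications of the second lumbar puncture, second PET scan and second MRI qualify on timing. The first lumbar puncture, PET scan and MRI come before dosing (sections 8.5.2 to 8.5.4), and section 16.4.6 presents pre-dose safety data separately. Only the second round counts here.

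**Step 3: which outputs depend on relatedness?** The safety endpoints in Protocol section 5.4.2 and SAP section 3.4 cover AEs and TEAEs (overall, by severity, or leading to termination), SAEs and, in the protocol only, solicited AEs. None uses relatedness. SAP section 5.7 lists no related-AE row and rules out statistical testing of safety data. What is left is the descriptive table in section 16.4.6 and the SUSAR route in section 18.6.

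**Step 4: illustrative size.** Inputs: 15 patients per arm (30 randomized 1:1) and an assumed per-patient rate p of a complication of the second lumbar puncture. Expected count per arm = 15p. Chance of at least one in an arm = 1 − (1 − p)^15.

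| Assumed p | Expected per arm | Chance of at least one |
|---|---|---|
| 10% | 1.5 | 79% |
| 20% | 3.0 | 96% |
| 30% | 4.5 | 99.5% |

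**Step 5: illustrative dilution.** Assume true drug-related AE rates of 40% (psilocybin) and 10% (niacin), with procedure events independent of drug events. Tabulated rate = 1 − (1 − drug rate)(1 − p). For p = 10%: 1 − 0.60 × 0.90 = 46% and 1 − 0.90 × 0.90 = 19%.

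| Assumed p | Psilocybin | Niacin | Ratio | Difference |
|---|---|---|---|---|
| 0 | 40% | 10% | 4.0 | 30 points |
| 10% | 46% | 19% | 2.4 | 27 points |
| 20% | 52% | 28% | 1.9 | 24 points |
| 30% | 58% | 37% | 1.6 | 21 points |

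The difference shrinks by the factor 1 − p. The ratio shrinks more, because the niacin rate starts low.

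**The case against.** The strongest reply is that this is a wording matter with a small reach. Section 16.4.6 speaks of relatedness to treatment and does not cite section 18.3. The CRF is not shown and may already hold separate items. Procedural events would remain recognisable by preferred term. The protocol elsewhere distinguishes the radioligand and procedures from the study drugs (sections 11.1 and 18.6). An ordinary post-puncture headache or haematoma would not normally be both serious and unexpected, and all SAEs are reported in any case.

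Much of this stands as a limit on size. It does not remove the problem: section 18.3 is the governing text, it states a rule that merges the causes, and a CRF built to follow it would have one field. Preferred terms do not resolve headache, which section 17.1.1 lists among the commonest psilocybin effects and section 17.6 lists as a lumbar puncture risk.

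Three stronger readings are tempting and not supported:

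- **That the related-AE comparison is a main safety result.** It is not a listed endpoint and nothing on it is tested.
- **That both lumbar punctures count.** At 10-30% per puncture, 1 − (1 − p)² gives 19-51% of patients, about 3-8 of 15. The first puncture is pre-dose and presented separately, so this does not describe the post-dose table.
- **That the solicited headache classes need a lumbar puncture category.** Section 18.1.3 says "these will be classified as a migraine, tension headache, or other headache", so there is a residual class. The synopsis collects solicited AEs only to Day 8, and Day 8 (15 − 7) is the earliest day for the second puncture, so the overlap is almost nil.

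**Conclusion.** The point holds in limited form. Section 18.3 merges two causes in one answer and labels every yes a suspected adverse reaction. Followed literally, it places complications of the post-dose procedures in the treatment-related AE table of both arms, and it lets a serious and unexpected procedural event be handled as a suspected reaction to the investigational product. Efficacy results and the listed safety endpoints are not affected.

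On an assumed 10-30% complication rate for the second lumbar puncture, about 1.5-4.5 of 15 patients per arm would be counted as related regardless of the drug. The documents supply neither that rate nor the 40% and 10% drug-related rates behind the dilution figures. The dilution looks large as a ratio (4.0 falling to between 2.4 and 1.6) and milder as a difference (30 points falling to between 27 and 21). The direction of the effect does not depend on these choices, provided that procedure events are about equally common in the two arms. The conclusion also assumes that the CRF follows the protocol wording.

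**What to change.** In section 18.3, replace the single question with three separate causality assessments for each AE: (a) psilocybin/niacin; (b) the radioligand; (c) a study procedure, naming which one (lumbar puncture, arterial cannulation, venepuncture, PET or MRI procedures). State in section 16.4.6 that the treatment-related AE table uses (a) only and that (b) and (c) are tabulated separately. State in section 18.6 that the SUSAR assessment for the investigational product uses (a) only.

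The cost is a few CRF fields, short edits to three protocol sections, and blinded re-coding of AEs already recorded. No extra visits or patient data are needed.
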